#### Preliminary Effectiveness Measures

Participants of both the intervention and control groups will complete 5 validated and reliable patient-reported outcome measures on the web at baseline and post program. This includes the following:

The Medical Issues, Exercise, Pain, and Social Support Questionnaire—a validated (eg, concurrent validity and construct validity) and reliable (eg, internal consistency) measure for perceived ability (eg, knowledge, skill, behavior, attitudes, and self-efficacy) to manage JIA [25].The Children’s Arthritis Self-Efficacy Scale—a validated (eg, concurrent validity and construct validity) and reliable (eg, internal consistency) measure for arthritis self-efficacy [26].The Pediatric Quality of Life Inventory 3.0 Rheumatology–Teen Module—a validated (eg, construct validity and concurrent validity) and reliable (eg, internal consistency) measure used for pediatric rheumatology–specific health-related quality of life in children aged 13-18 years [27].The PROMIS (Patient-Reported Outcomes Measurement Information System) Pediatric Pain Interference Scale—a validated (eg, concurrent validity and construct validity) and reliable (eg, internal consistency) measure for pain behavior in children aged 8-17 years [28].Readiness for Adult Care in Rheumatology—a validated (eg, concurrent validity and construct validity) and reliable (eg, internal consistency) measure to assess transition readiness in adolescents with JIA [29].

### Ethical Considerations

This study was approved by the Conjoint Health Research Ethics Board of the University of Calgary (REB22-1820), Edmonton (pSite00000101), Vancouver (H24-02469), SickKids Research Ethics Board (1000080939), and the Health Research ethics Board of the University of Manitoba (HS26016{H2023:168}). Informed consent will be obtained from all participants in accordance with the tenets of the Declaration of Helsinki, with parental consent required for minors. Participants will be informed of their right to opt out at any time. Data collected will be anonymized to ensure privacy and confidentiality, with protective measures in place to safeguard the participants’ information. Compensation for participation will be provided in the form of gift cards valued at CAD $50 (US $36.51) per participant. No identification of individual participants will be possible in any images or supplementary material included in the manuscript.

### Data Analysis and Statistical Methods

#### Sociodemographic Characteristics

Descriptive statistics (mean, SD, and IQR) will be used to analyze sociodemographic characteristics.

#### Data Analysis Plan

##### Feasibility Outcomes

The feasibility of the SMP will be analyzed using descriptive statistics (eg, mean, SD, and frequencies) based on (1) adherence with the SMP (defined as 80% when the participant completes 4 sessions over 8 weeks), (2) recruitment and withdrawal rates, and (3) the proportion of completed questionnaires at baseline and 4 weeks after the last session (defined as 80% when all measures completed).

This study will use qualitative thematic analysis [30,31] to analyze the data. The experiences, perceptions, and satisfaction measured through video-recorded semistructured individual interviews will be transcribed verbatim and entered to a data analysis software (NVivo version 12.0; Lumivero) [32] for analysis. This method involves iterative cycles of coding, interpreting, and reflecting on the data to identify patterns and themes that capture participants’ experiences and perceptions of SMP. Key nonverbal cues, terms, and phrases will be noted and underlined in the transcript and coded accordingly. All qualitative data will be read separately several times by the research assistant and at least 2 investigators to obtain an overall understanding of the data, generate initial codes, and develop themes based on research questions. The themes will be refined, defined, and supported by extracts from the transcript. Finally, the themes will be documented in a manuscript.

This study will ensure rigor and trustworthiness through credibility, transferability, dependability, confirmability, and reflexivity [33]. A detailed description of the study setup, participants, and data collection procedures will support transferability. Dependability will be ensured by documenting data collection, analysis, and interpretation. Two researchers will independently code transcripts and resolve discrepancies through consensus. A single interview schedule will guide all interviews, and member-checking will enhance credibility. A reflective journal will document research discussions as part of the audit trail. In addition, verbatim transcripts of participants’ responses will be included in the manuscript to ensure confirmability [33]. Using the same qualitative methods, we will evaluate intervention fidelity of the recorded video sessions. Scores from the developed fidelity checklist will be used to further support the evaluation of intervention fidelity. Positive checklist ratings (scale 0-10, where 10 is the most positive) will indicate an intervention that is delivered consistently and as planned.

##### Preliminary Effectiveness Outcomes

The quantitative data will be entered into SPSS [34]. Descriptive statistics will be used to analyze the patient-reported outcome measures with an ordinal Likert scale at baseline and immediately post intervention. In addition, nonparametric Wilcoxon signed rank tests will be used to assess if there is a significant difference between a pre- and posttest outcome. Nonparametric tests will be used due to the small sample size and a lack of normally distributed data. Changes in pre- and posttest outcomes will be analyzed over time using a repeated measures mixed linear model approach where participants will be included as the random effect and baseline scores, study site, and disease-related characteristics will be used as fixed factors or covariates.

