**Objective:**

The aim of this pilot randomized controlled trial (RCT; the VISTA-JIA trial) is to evaluate the feasibility and preliminary effectiveness of a virtual group-based SMP for adolescents with JIA in comparison to a waitlist control group.

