## Methods

### Study Design

A pilot RCT will be conducted to determine the feasibility and preliminary effectiveness of a virtual SMP intervention. Eligible participants will be randomized 1:1 to either the intervention group or a waitlist control group. Both groups will complete baseline measures (T0) as well as postprogram measures (T1). Participants enrolled into the intervention will undergo the SMP and be asked to participate in an optional postintervention interview. The waitlist control group will continue receiving standard of care during this program period. They will be given the option to complete the SMP afterwards, and if completed, be asked to complete postintervention questionnaires. They will also be asked to participate in the optional postintervention interview. The study is registered in ClinicalTrials.gov (NCT06184100). Figure 1 shows the trial schema, and Multimedia Appendix 1 shows the timeline. This study follows the SPIRIT (Standard Protocol Items: Recommendations for Interventional Trials; checklist provided in Multimedia Appendix 2) guidelines.

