### Randomization, Recruitment, and Sample Size

CONSORT (Consolidated Standards of Reporting Trials; checklist provided in Multimedia Appendix 3) 2010 guidelines suggest a sample size calculation of 9% of the anticipated full-scale RCT for the intervention group in pilot studies [22,23]. However, to establish feasibility at several sites and get an estimate of a statistically significant SD to inform a full-scale multicenter trial, our target is to conduct 2 offerings of the program with 4-6 participants per group at each of the 5 sites to control for site-specific education. Eligible participants will be identified through a review of the patient database and will be contacted by research coordinators. Some participants will also be recruited during their clinic visits. They will receive detailed information about the study, including its objectives, procedures, and potential benefits. Interested participants will provide informed consent (or assent, with parental consent for minors). The study aims to recruit a total of 100 participants. Therefore, we will require 50 participants in the intervention group and 50 in the waitlist control group. This sample size was chosen to establish feasibility and inform a larger multicenter trial. Participants will be randomized 1:1 to either the intervention group or the waitlist control group using block randomization with variable block sizes. This randomization will be conducted using REDCap (Research Electronic Data Capture; Vanderbilt University), a secure web-based application for managing data. Randomization will occur before baseline measures are completed. Participants in the intervention groups will be from the same center to adapt the program to local health care systems and account for the variability of nonformal educational practices between centers. This approach will also facilitate an evaluation/subgroup analysis of outcome measures at each center.

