#### Missing Data Considerations

We will examine patterns of missing data, determine demographic and/or clinical characteristics that are related to missing data at study time points, and the potential impact on the primary findings. Patterns will be used to inform our use of an intention to treat and to determine if including a per protocol approach in the full-scale RCT will be appropriate.

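### The effectiveness analysis states no main comparison between the randomised arms, although the objective is effectiveness against a waitlist

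*Protocol article*

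**What the plan says.** The Objective in the abstract, repeated at the end of the Introduction, is to evaluate "feasibility and preliminary effectiveness of a virtual group-based SMP for adolescents with JIA in comparison to a waitlist control group". Under Study Design, "Eligible participants will be randomized 1:1 to either the intervention group or a waitlist control group", and both arms complete questionnaires at T0 and T1. The sample size section plans 50 participants per arm. Preliminary Effectiveness Measures confirms that both arms complete all five instruments at both times.

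The analysis is under Preliminary Effectiveness Outcomes and has three parts:

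- descriptive statistics at baseline and after the intervention;
- a paired test: "nonparametric Wilcoxon signed rank tests will be used to assess if there is a significant difference between a pre- and posttest outcome";
- a repeated measures mixed linear model of change over time, with participant as the random effect, in which "baseline scores, study site, and disease-related characteristics will be used as fixed factors or covariates".

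The Methods paragraph of the abstract adds only that descriptive statistics and nonparametric tests will be used. Subgroup Analysis plans exploratory interaction tests of the intervention's effectiveness by site and patient characteristics. No section names a two-sample test, a main effect of arm or a between-arm estimate.

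**The concern.** The comparator in the objective is the waitlist arm. The waitlist exists to remove whatever moves scores without the SMP: passage of time, regression to the mean, usual care, and answering the same questionnaire twice. A pre/post test within participants removes none of these. A model of change over time without an arm term does not either.

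An analyst who follows the section literally could report significant improvement after the SMP when the SMP had no effect. The article already anticipates preliminary improvements in self-management skills, self-efficacy and transition readiness, and says that the pilot will inform a full-scale trial. That trial would then inherit pre/post changes where it needs an estimate of the randomised effect.

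**Working it through.** **1. The plan's own figure.** Five sites × 2 offerings × 4 to 6 participants gives 40 to 60 in the SMP arm. At 5 per group, 5 × 2 × 5 = 50, and 2 × 50 = 100 in total. The stated sample size reproduces. No alpha, power, effect size or SD is given for the effectiveness scores, so there is no power figure to reproduce.

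**2. What each analysis estimates.** Let δ be the change that would occur in either arm without the SMP, and τ the SMP effect.

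- Signed rank test in the SMP arm: tests δ + τ = 0.
- Signed rank test in the waitlist arm: tests δ = 0.
- Signed rank test with both arms pooled in equal numbers: average change δ + τ/2.
- Mixed model with the listed terms plus time: the time effect is again the pooled change.
- Difference between arms in change, or in T1 adjusted for T0: estimates τ.

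Only the last line answers the objective, and it is the one that is not stated.

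**3. Size when τ = 0.** Assumptions, none from the documents: normal change scores, the same drift d in both arms in units of the SD of the change score, 50 per arm, two-sided 5%.

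The large-sample power of the signed rank test for normal data is about Φ(d√(3n/π) − 1.96). For n = 50, √(3 × 50/π) = 6.91.

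| d | 6.91 × d | Approximation | Simulated, SMP arm |
|---|---|---|---|
| 0.2 | 1.38 | Φ(−0.58) = 28% | about 27% |
| 0.3 | 2.07 | Φ(0.11) = 54% | about 53% |
| 0.4 | 2.76 | Φ(0.80) = 79% | about 78% |

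At d = 0.1 the rate is about 11%. Pooling both arms (n = 100) raises it to about 49% at d = 0.2 and 84% at d = 0.3. In the same simulations a between-arm rank test on the change scores rejects in about 5% of trials, whatever the drift.

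**4. What the sample supports once the contrast is stated.** For a T1 comparison adjusted for T0, with 80% power and two-sided 5%, the detectable standardised difference is (1.96 + 0.84) × √(1 − ρ²) × √(2/50), where ρ is the assumed T0–T1 correlation:

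- ρ = 0: 2.80 × 1 × 0.20 = 0.56
- ρ = 0.5: 2.80 × 0.866 × 0.20 = 0.49
- ρ = 0.7: 2.80 × 0.714 × 0.20 = 0.40

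These figures ignore clustering within SMP groups, which would make them larger. The planned sample can therefore give a usable, if imprecise, randomised estimate.

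**The case against.** The strongest defence is that silence is not exclusion. The list of model terms is visibly incomplete: it omits time as well, in a model said to analyse change over time. It may name only the random effect and the adjustment covariates. The subgroup section refers to the intervention's effectiveness by site and patient characteristics, which in a trial measuring both arms naturally implies an arm term. A reader might infer that the investigators have ruled out comparing the arms, or that the trial cannot do so. The documents support neither: both arms are measured at both times, and even the planned descriptive statistics would allow an unadjusted difference to be worked out.

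That limits the point without removing it. The article does more than leave a detail to an analysis plan. It picks a test, gives reasons for it and lists model terms, and none of this contrasts the arms. The subgroup interactions are exploratory and yield no overall arm effect.

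The defence is also right that effectiveness is secondary and preliminary here. The primary outcome is adherence, and the Significance section leaves demonstration of effectiveness to a larger trial.

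Two further inferences go beyond the text. One is that baseline is wrongly used as both outcome and covariate; that is only one reading, since the model could be of change scores adjusted for baseline. The other is that the analysis population depends on the data, from "Patterns will be used to inform our use of an intention to treat"; that sentence continues to the full-scale trial and can be read as concerning it.

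**Conclusion.** The point holds in this form: the effectiveness section states no main between-arm contrast, so as written the plan does not estimate effectiveness "for adolescents with JIA in comparison to a waitlist control group". This follows from the text and needs no assumption.

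The size does rest on assumptions. With no SMP effect and a common drift of 0.2, 0.3 or 0.4 SD of the change score, the SMP-arm signed rank test is significant in about 27%, 53% and 78% of trials, against about 5% for a between-arm test. With smaller drift the problem shrinks (about 11% at 0.1 SD), and with no drift it disappears. Nothing in the documents shows which value applies.

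The secondary effectiveness objective is affected. The primary adherence outcome and the other feasibility outcomes are not.

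**What to change.** Reword Preliminary Effectiveness Outcomes. For each of the five scores, make the main estimate the adjusted between-arm difference at T1 with its 95% CI, from a linear model of the T1 score on randomised arm, T0 score and site. Analyse participants in their allocated arm. Use only T0 and T1 data from the randomised period; the questionnaires that waitlist participants complete after taking the SMP later do not belong in this comparison. This model needs both scores, so say how a missing T0 or T1 is handled.

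Alternatively, use a mixed model with T0 and T1 as outcomes, a common baseline mean and arm-by-time, without entering T0 again as a covariate. This also retains participants who have only one of the two scores.

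Keep the signed rank tests, if wanted, as within-arm description only, and state in Subgroup Analysis that the interactions are with randomised arm.

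The cost is one paragraph. It needs no new data and no change in sample size, and it can be made before analysis. The downside is that p-values will look less favourable than those from pre/post tests.

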**Methods:**

A total of 100 participants with confirmed JIA (aged 12-17 years) will be recruited from 5 Canadian pediatric rheumatology centers and randomized 1:1 to the intervention or waitlist control groups. Adolescents in the intervention group will receive the virtual SMP. Those randomized to the control group will receive standard of care alone and will later be eligible for the SMP. The SMP includes JIA disease education, self-management strategies, and peer support. Four 60- to 90-minute sessions will be conducted over 8 weeks with a group size of 4-6 participants. The primary feasibility outcome will be adherence to the SMP (defined as completion of all 4 sessions by at least 80% of participants). Other secondary feasibility outcomes will include recruitment and withdrawal rates, the proportion of completed questionnaires, engagement and satisfaction with the SMP measured through a semistructured virtual interview, and intervention fidelity (consistent content and technology delivery). Secondary preliminary effectiveness outcomes will be assessed by completing 5 validated questionnaires at pre- and postprogram time points: (1) the Medical Issues, Exercise, Pain, and Social Support Questionnaire to assess perceived ability to manage JIA (self-management); (2) the Children’s Arthritis Self-Efficacy Scale to assess self-efficacy; (3) the Pediatric Quality of Life Inventory 3.0 Rheumatology–Teen Module to assess health-related quality of life; (4) the PROMIS (Patient-Reported Outcomes Measurement Information System) Pediatric Pain Interference Scale to assess pain interference; and (5) Readiness for Adult Care in Rheumatology to assess transition readiness. Descriptive statistics and nonparametric tests will be used to analyze the data.

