#### Data Integration

To address the main research questions related to feasibility and primary effectiveness for scale-up, we will integrate qualitative and quantitative data using a convergent parallel design [35]. This method involves the simultaneous collection and separate analysis of both data types, followed by merging the results for comprehensive insights. Quantitative data from validated questionnaires will provide measurable outcomes on self-management, self-efficacy, health-related quality of life, pain interference, and transition readiness. Concurrently, qualitative data from semistructured virtual interviews will capture participants’ experiences, engagement, and satisfaction with the SMP. By comparing quantitative results with themes from the qualitative analysis, we will identify patterns, discrepancies, and complementary findings. This holistic approach ensures that both numerical trends and personal narratives are considered together, offering a robust understanding of the program’s feasibility and effectiveness, which will inform potential scale-up and integration into routine clinical practice.

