### Significance

This will be the first, to our knowledge, evidence-based self-management program to offer virtual self-management participation for adolescents with JIA. If proven feasible and acceptable, this SMP will be then tested in a larger RCT with enough participants and statistical power to demonstrate the effectiveness of the SMP across pediatric rheumatology centers in Canada. The program’s unique design to include both health care providers (HCPs) and peer participants within a group setting, provides an opportunity to (1) enhance and instill confidence in participants’ individual ability to self-manage skills under the guidance of experienced HCPs; (2) allow for participants to gain a better understanding of JIA through questions and input provided by their peers; (3) enhance their emotional management skills by learning through the shared challenges and emotional perspectives of participants within the group; (4) potentially foster a network of social support among the participants, which may prove beneficial beyond the scope of this project and their transition to adult care; and (5) streamline the need for HCPs’ educational practices and optimize for consistent dissemination of information with engaging and interactive activities. Additionally, assessing intervention fidelity will allow us to establish a standardized framework for content and technology delivery and will help to train future session facilitators. This will finally be applicable to broader audiences as our establishment of a standardized technology-delivery framework and guidance for effective virtual communications in a group setting can be applied to any virtually delivered intervention in health care.

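### The two analyses given for the five effectiveness questionnaires do not fit together, the mixed model is mis-specified for two time points, and neither names randomised arm

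*Protocol article*

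**What the plan says.** The Protocol article, Preliminary Effectiveness Outcomes, describes two analyses of the same before-and-after questionnaire scores.

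- The first is a within-person test: "nonparametric Wilcoxon signed rank tests will be used to assess if there is a significant difference between a pre- and posttest outcome". The reason given is "Nonparametric tests will be used due to the small sample size and a lack of normally distributed data".
- The second follows directly: "Changes in pre- and posttest outcomes will be analyzed over time using a repeated measures mixed linear model approach". Participant is the random effect. The fixed factors or covariates listed are baseline score, study site and disease-related characteristics. Randomised arm is not in that list.

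The abstract's Methods paragraph mentions no model: "Descriptive statistics and nonparametric tests will be used to analyze the data". Study Design gives two assessments in the randomised period, T0 and T1. Waitlist participants who later take the programme are asked for a further questionnaire.

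On the standing of these outcomes, the abstract says "Secondary preliminary effectiveness outcomes will be assessed by completing 5 validated questionnaires at pre- and postprogram time points" and "The primary feasibility outcome will be adherence to the SMP". Data Integration, however, opens "To address the main research questions related to feasibility and primary effectiveness for scale-up". The Significance section puts the next step this way: "If proven feasible and acceptable, this SMP will be then tested in a larger RCT".

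**The concern.** The article has three defects on this point, all in what it states.

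1. **The reason and the second method do not match.** If small numbers and non-normality rule out parametric methods, a linear mixed model on the same scores needs its own justification. If the model is acceptable, the reason for the rank test weakens. The abstract names only the first approach.
2. **The mixed model cannot be fitted sensibly as listed.** With two time points, the baseline score is either an outcome row or a covariate. Using it as both distorts the standard error. Using it only as a covariate leaves one row per person.
3. **Neither analysis names the randomised comparison.** The objective is a comparison with a waitlist control. A pre/post test in one arm, or a time effect without arm, also picks up anything that moves both arms: regression to the mean, routine care, or answering the same questionnaire twice.

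At stake are the effectiveness estimates that are meant to inform the full-scale trial. The word *primary* in Data Integration adds to this, because it gives these results more standing than the abstract does.

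**Working it through.** **Inputs.** From the article: five questionnaires; 50 participants per arm; T0 and T1. The article states no alpha, so 0.05 two-sided is assumed. Pre/post correlation r, between-outcome correlation and drift are also assumptions, with ranges shown. Scores are standardised to variance 1 at both times.

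**Step 1: T0 as both outcome row and covariate.** The rows are T0 and T1, with T0 as covariate. The slope on T0 is 1 in the first row and r in the second, so the common slope is (1+r)/2.

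- Residual, row T0: T0·(1−r)/2, with variance (1−r)²/4.
- Residual, row T1: T1 − T0·(1+r)/2, with variance 1 − r(1+r) + (1+r)²/4.
- Covariance of the two: (1−r)/2 × (r−1)/2 = −(1−r)²/4.

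The covariance is negative for every r below 1. A random-intercept variance cannot be negative, so it is estimated as zero and the model treats the two rows as independent. The modelled variance of the change is then the sum of the two residual variances, while the true variance is 2(1−r). The ratio simplifies to (3+r)/4, and the true size of a nominal 5% test of time is 2·[1 − Φ(1.96·√((3+r)/4))].

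At r = 0.5 the residual variances are 0.0625 and 0.8125, and the covariance is −0.0625. The modelled change variance is 0.875 against a true 1.0. The size is 2·[1 − Φ(1.833)] = 6.7%.

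| r | (3+r)/4 | Size, formula | Size, simulation (4000 null trials) |
|---|---|---|---|
| 0.3 | 0.825 | 7.5% | 7.7% |
| 0.5 | 0.875 | 6.7% | 6.7–7.0% |
| 0.7 | 0.925 | 5.9% | 6.5% |

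**Step 2: only T1, or only the change score, as outcome.** There is one row per person. Participant variance and residual variance enter only as a sum, so they cannot be separated.

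**Step 3: change common to both arms.** Assume r = 0.6 and a drift of 0.2 SD in both arms with no treatment effect. The SD of the change is √(2 × 0.4) = 0.894, so the standardised drift is 0.2/0.894 = 0.224. With 50 people the expected test statistic is 0.224 × √50 = 1.58. A paired test at 5% is then significant with probability about Φ(1.58 − 1.96) = 35% for one outcome. Over five outcomes with between-outcome correlation 0.5, the simulation (4000 runs) gave at least one significant intervention-arm signed rank test in 68% of runs. A baseline-adjusted between-arm model gave 19%. That is about its rate without drift (18%), because shared drift cancels between arms.

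**Step 4: five tests with no change at all.** If independent, 1 − 0.95⁵ = 22.6%. Simulated rates for at least one significant intervention-arm signed rank test run from about 22% (between-outcome correlation 0) to about 13% (correlation 0.8).

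**The case against.** The case for leaving the text alone has several parts.

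- **A rank test followed by an adjusted model is a common pairing**, and a linear model needs roughly normal residuals, not normal raw scores. This is fair, and it makes the mismatch of reason and method the mildest of the three defects. The article does not make that argument, however, and its abstract drops the model.
- **The model sentence is condensed, and arm may be intended.** The objective is comparative, and the Subgroup Analysis section speaks of interaction tests for intervention effectiveness. A reader might infer that the trial has no between-arm analysis at all. The documents do not support that, since a fuller plan may contain one. What stands is that the article lists the model's terms and arm is not among them.
- **Some waitlist participants have a third assessment.** True, but it is optional, comes after they have received the programme, and does not help the randomised T0–T1 comparison.
- **An excess size of one to three percentage points is small.** This also stands. The missing arm term matters more.
- **No lead outcome or multiplicity rule is required here.** Agreed. These are secondary outcomes of a pilot, and such rules commonly sit in an analysis plan that is not shown.

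Two stronger readings are tempting. One is that a chance significant result is likely. At about 13 to 22% for five intervention-arm tests it is above nominal but well under one half, and it rests on an assumed alpha. The other is that a significant questionnaire result would trigger scale-up. Data Integration sets no such rule, and the Significance section rests the larger trial on feasibility and acceptability.

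**Conclusion.** The point holds as a defect of specification. The article gives two analyses of the same outcomes whose rationales do not agree. The second is mis-specified for two randomised time points on either reading: true size about 6 to 8% instead of 5% for r between 0.7 and 0.3, or a participant effect that cannot be estimated. The more consequential gap is that neither analysis, as listed, compares the randomised arms. The 68% against 19% contrast illustrates this under an assumed 0.2 SD drift; it does not forecast this trial. The word *primary* in Data Integration is a wording conflict with the abstract and the Significance section, nothing more. The trial's primary outcome, adherence, is unaffected.

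**What to change.** 1. In Preliminary Effectiveness Outcomes, make one analysis per questionnaire the inferential one: a linear model of the T1 score on randomised arm, T0 score and site, reporting the adjusted between-arm difference with a 95% CI. If normality is a worry, check the model residuals.
2. Keep the signed rank tests, if wanted, as descriptive summaries within arm, without significance claims.
3. Label all five outcomes exploratory. Naming one lead outcome is the sponsor's option.
4. Align the last sentence of the abstract's Methods paragraph with this analysis.
5. In Data Integration, replace *primary* by *preliminary* before effectiveness.

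One caution: the article has randomisation take place before the baseline measures are completed. The text should say whether T0 is answered before participants learn their allocation, since the adjustment relies on T0 not being affected by it.

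The cost is a few sentences before analysis, with no new data and no burden on participants. The pilot gives up significance claims from the within-arm tests.
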